
### 8.2.2 Other Expected Serious Adverse Events in current trial

Patients in the current trial are critically ill and are included early in what is expected to be a prolonged hospital stay, often in intensive care unit and with several interventions over many days or even weeks. Both the standard care prior to arrival in hospital and during their stay have significant risks for adverse events. Below is a table of expected serious adverse events. These will be recorded in the CRF, but not reported to Sponsor, see flow chart section 8.5.

| Expected Serious Adverse Events                 |                                                                                                                                                                                                                                                                        |
|-------------------------------------------------|------------------------------------------------------------------------------------------------------------------------------------------------------------------------------------------------------------------------------------------------------------------------|
| System Organ Class (MedDRA)                     | Expected event                                                                                                                                                                                                                                                         |
| Blood and lymphatic system disorders            | 
 
• Methemoglobinemia
 
                                                                                                                                                                                                  |
| Cardiac disorders                               | 
 
• Cardiac arrest
 
• Myocardial infarction
 
• Ventricular fibrillation
 
• Ventricular tachycardia
 
• Bradycardia
 
                                                                      |
| Immune system disorders                         | 
 
• Acute anaphylaxis
 
                                                                                                                                                                                                  |
| Infections and infestations                     | 
 
• Acute infection
 
                                                                                                                                                                                                    |
| Injury, poisoning and procedural complications  | 
 
• Iatrogenic pneumothorax
 
• Incision site bleeding
 
• Anaesthesia intubation complication
 
                                                                                                           |
| Nervous system disorders                        | 
 
• Brain hypoxia
 
                                                                                                                                                                                                      |
| Renal and urinary disorders                     | 
 
• Hypoxic kidney injury
 
• Renal failure
 
                                                                                                                                                                     |
| Respiratory, thoracic and mediastinal disorders | 
 
• Aspiration
 
• Pneumonia
 
• Pneumothorax
 
• ARDS
 
• ALI
 
                                                                                                                             |
| Skin and subcutaneous tissue disorders          | 
 
• Pressure wounds
 
                                                                                                                                                                                                    |
| Surgical and medical procedures                 | 
Events classified under MedDRA high level term:
 
 
• Anaesthesia and allied procedures
 
• Venous therapeutic procedures
 
• Arterial therapeutic procedures
 
• Therapeutic procedures NEC
 
 |
| Vascular disorders                              | 
 
• Acute hypotension
 
                                                                                                                                                                                                  |

Please note: Both suspected rebound reactions and death prior to end of intervention will always be reported to Sponsor as a serious adverse event.

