In terms of safety, Cochrane reports a statistically significant increase in renal failure in the INO groups. Interestingly this adverse event is not noted in the SPC chapter 4.8 Undesirable effects. The Cochrane analysis includes studies on this adverse event in patients admitted to hospital and intensive care units. A systematic review from 2015 finds a dose- response relationship between INO and renal failure. A reduced dose and length of INO treatment reduces the risk of kidney failure(10)

In Scandinavian guidelines for the treatment of ARDS they advise against routine use of INO, but recognize that INO may be used as a rescue measure to temporarily increase oxygenation in patients with catastrophic hypoxemia and imminent risk of death (weak recommendation, moderate quality of evidence)(11). The literature has described INO being used as rescue strategy in severe ARDS attributable to 2009 H1N1 influenza(12).

For prehospital use of INO as emergency treatment to improve oxygenation prior to intubation there are no literature available. A PubMed central search 31. March 2020 yields no results for: "Rapid Sequence Induction and Intubation"[Mesh] AND "Nitric Oxide"[Mesh].

Recent experience during the COVID-19 pandemic indicates a need for additional measures to rapidly improve oxygen saturation for safe transport or rapid sequence induction, intubation and mechanical ventilation. As a direct consequence of this situation, a standard operating procedure for pre-hospital INO as a rescue therapy for patients with COVID-19, has been implemented at Oslo University Hospital. We also want to explore this option in a trial setting, as the evidence is inconclusive.

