### **Renal toxicity**

Renal impairment is a well described complication to INO, although it is not described in the SPC. All previous studies in adults are in intensive care unit patients, who are exposed to INO, often over several days, and much longer than patients are exposed to IMP in the current trial. We will evaluate renal function in all included patients using the Kidney Disease: Improving Global Outcomes (KDIGO)(16)

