## 8.5 Reporting Procedure

Then flow chart describes the SAE reporting procedure:

[figure not shown]

Unexpected SAEs must be reported by the investigator to the sponsor, [name], using the Oslo University Hospital reporting system Achilles, within 24 hours after the site has gained knowledge of the unexpected SAE. Sponsor should also be notified via telephone or SMS at [name] when a report is sent.

Every SAE must be documented by the investigator on the SAE pages as part of the CRF. The Serious Adverse Event Report Form must be completed, signed and sent to [name]. The initial report shall promptly be followed by detailed, written reports if necessary. The initial and follow-up reports shall identify the trial subjects by unique code numbers assigned to the latter.

The sponsor keeps detailed records of all SAEs reported by the investigators and performs an evaluation with respect to seriousness, causality and expectedness.

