## **8.7 Data Monitoring Committee (DMC)**

A DMC will be recruited. Their work will be described in a charter based on the NORCRIN Standard Operating Procedure. This describes the roles and responsibilities of the DMC, including the timing of meetings, methods of providing information to and from the DMC, frequency and format of meetings, statistical issues and relationships with other Sponsor. The charter and the DMC should be in place before the first patient is included.

The DMC will meet after the interim analysis, and in the event of SUSAR reporting.

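### The written rule in 8.2.2 keeps listed 'expected' SAEs from the sponsor even when they are suspected to be related to INO, apart from suspected rebound and death before end of intervention

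*Protocol*

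**What the plan says.** Section 8.2.2 of the protocol tabulates serious events expected in critically ill patients and states: "These will be recorded in the CRF, but not reported to Sponsor, see flow chart section 8.5". The renal row includes "Renal failure". A note below the table gives the exceptions: "Both suspected rebound reactions and death prior to end of intervention will always be reported to Sponsor as a serious adverse event".

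Section 8.5 sets the expedited duty, with a 24-hour limit from the site's knowledge of the event: "Unexpected SAEs must be reported by the investigator to the sponsor". On the sponsor's part it says: "The sponsor keeps detailed records of all SAEs reported by the investigators and performs an evaluation with respect to seriousness, causality and expectedness".

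On renal harm, section 7.2 says: "Renal impairment is a well described complication to INO, although it is not described in the SPC". Section 1.2.2, after noting a significant increase in renal failure in a Cochrane review, adds: "Interestingly this adverse event is not noted in the SPC chapter 4.8 Undesirable effects".

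Section 8.7 on the DMC says: "The DMC will meet after the interim analysis, and in the event of SUSAR reporting".

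**The concern.** Two meanings of 'expected' are mixed. One is that the event is likely in a patient this ill. The other is that the event is a known reaction to the product. The first is a fair reason to spare the sponsor a stream of disease-related reports. The second is the one that matters for deciding whether a suspected reaction is a SUSAR. Section 8.2.2 uses the first meaning to decide whether the sponsor is told at all, and does not ask whether the investigator suspects INO.

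What is at stake is prompt individual-case review. The sponsor evaluates causality and expectedness on the SAEs that investigators report, and the SUSAR time limits in 8.5.1 run from the sponsor's knowledge. A suspected reaction held back by the list would start neither. Renal failure is the clearest case, because the protocol names it as an INO effect missing from the SPC and then puts it on the list that is not reported.

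**Working it through.** There is no plan figure to reproduce, and no sample-size or error-rate arithmetic applies. The check sets the provisions side by side.

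1. **What counts as a reaction.** Section 8.1.3 treats an event as an adverse reaction when its causal link to the IMP is rated certain, probable/likely or possible. Section 8.4 has causality rated on the WHO-UMC scale and recorded in the CRF. The information needed to sort listed events by suspected relatedness is therefore already collected.

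2. **What counts as a SUSAR.** Section 8.1.4 requires a serious reaction that is unexpected and possibly related to INO.

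3. **Who is told.** The rule in 8.2.2 turns on membership of the list, and the 24-hour duty in the 8.5 text turns on unexpectedness. Neither uses the causality rating. The note under the 8.2.2 table makes two exceptions: suspected rebound, which is an INO reaction, and death before end of intervention. No other related event is excepted.

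4. **List against product information.** Count of named events in 8.2.2 by organ class: blood 1, cardiac 5, immune 1, infections 1, injury and procedural 3, nervous system 1, renal 2, respiratory 5, skin 1, vascular 1. The sum is 1 + 5 + 1 + 1 + 3 + 1 + 2 + 5 + 1 + 1 = 21, plus four MedDRA high-level terms under surgical and medical procedures. Compared with the SPC 4.8 table in 8.2.1:
   - Three match: methemoglobinemia, bradycardia (in the SPC only after abrupt discontinuation) and hypotension.
   - 21 − 3 = 18 do not match, or 17 if brain hypoxia is counted as the SPC's hypoxia.
   - Among those absent are renal failure, hypoxic kidney injury, cardiac arrest, myocardial infarction, ventricular fibrillation, ventricular tachycardia and anaphylaxis.

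5. **Worked case.** Suppose a non-fatal renal failure meets the SAE definition and is rated possibly related. It is an adverse reaction under 8.1.3. It is absent from the SPC table, so judged against the SPC it would be unexpected and would fit 8.1.4. Under 8.2.2 it is a listed event, so it is recorded and not reported. The sponsor evaluation in 8.5 covers reported SAEs, so on this text the case does not reach it.

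6. **A possible conflict inside 8.5.** The section also has every SAE documented on the CRF's SAE pages, and the next sentence has the SAE Report Form completed, signed and sent to a recipient whose name is removed. If that covers listed events and the recipient acts for the sponsor, it contradicts 8.2.2. If it covers only unexpected SAEs, the gap in step 5 stands. The text does not settle which.

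**The case against.** The strongest objection is that the governing flow chart has not been seen. The exemption sentence refers to it, and 8.5 presents it as the description of the procedure. A causality step may be there. That stands as a limit: the finding concerns the written text. If the chart has such a step, the text of 8.2.2 and 8.5 still needs to say so.

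The design is also deliberate. The opening of section 8 explains that every participant is expected to meet a seriousness criterion, and it cites precedent for prespecifying outcomes. That justifies relief for disease-related events. It does not explain why events suspected to be caused by INO should share it.

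Renal harm is not left to case reports. Serum urea and KDIGO stage up to day 28 are safety endpoints, and severe kidney failure is an exclusion. Section 7.2 adds that earlier adult exposure often lasted days, against about one hour planned here. This lowers the expected frequency and means the data are not lost, but endpoint collection at follow-up is not prompt case review. Section 6.2 provides for unblinding when a serious reaction to the IMP is suspected, but attaches no reporting duty to it.

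A reader might go further than the documents allow in four ways:

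- **That a related listed event can never become a SUSAR.** This cannot be known with the chart unseen and the Report Form sentence open. Nor does the protocol say that the sponsor judges SUSAR expectedness by the 8.2.2 list; 8.2.1 separately gives the product's expected events.
- **That no related event is reported.** Suspected rebound always is, and so is a cardiac arrest that is fatal before end of intervention.
- **That 27 of 54 patients (27 / 2 = 13.5 per arm) are treated before anyone sees these events.** That is the interval to the planned safety interim in 10.4. It does not measure this gap. The study team, data management, the study monitor and the medical monitor all handle CRF safety data earlier.
- **That the DMC cannot meet otherwise, or will not see listed events by arm.** Section 8.7 leaves meeting timing and frequency to a charter that is not shown.

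**Conclusion.** The point holds for the protocol's written text. A listed serious event that is suspected to be related to INO, and is neither a suspected rebound nor a death before end of intervention, can miss prompt sponsor review and SUSAR assessment. The scope is 18 of 21 named events (17 on the generous match) that are on the non-reporting list but absent from the SPC table, with renal failure the case the protocol's own background makes hardest to defend.

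The number of patients affected cannot be derived, because the documents give no rates for related events. For events first learned of at the day-28 review, the 24-hour limit would run only from that point, so the gain there is case assessment more than speed.

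The conclusion assumes that the unseen flow chart adds no causality step and that the Report Form sentence in 8.5 does not already send listed events to the sponsor. If either assumption fails, what remains is a contradiction in the reporting instructions that sites cannot follow as written. Either way the text needs correcting, since it governs expedited safety reporting.

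**What to change.** - In 8.2.2, limit the exemption to listed events not suspected to be related to the IMP, and keep the two existing exceptions.
- In 8.5, require any SAE rated certain, probable/likely or possible to go to the sponsor within the existing 24-hour limit, whatever its term.
- State that expectedness for SUSAR purposes is judged against the SPC as reproduced in 8.2.1, and that the 8.2.2 list serves only to relieve reporting of unrelated events.
- Reconcile 8.2.2, the 8.5 text (including which SAEs the Report Form sentence covers) and the flow chart.

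The cost is a wording change and a modest number of extra SAE reports. The causality rating is already recorded, so no new data are needed, and listed events not suspected to be related stay exempt.

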### 8.3 Time Period for Reporting AE and SAE

- For each patient the standard time period for collecting and recording AE will be from allocation and until End of Intervention
- For each patient the standard time period for collecting and recording SAE will be from allocation and until the 28 day follow up visit. At the 28 days visit an assessment will be made where we specifically ask for all SAEs mentioned in chapter 8.2. We will also assess discharge notes and treating physician for other events that fulfil the SAE definition and that can be assessed by the study team.
- For patients still admitted to hospitals at day 28 an effort will be made to secure access to main discharge note for assessment for any SAE that has occurred between day 28 and discharge.
- Any information that comes to investigators attention for any included patient prior to End of Trial will be assessed according to this protocol

### 8.4 Recording of Adverse Events

If the patient has experienced adverse event(s), the investigator will record the following information in the CRF:

- The nature of the event(s) will be described by the investigator in precise standard medical terminology
- The duration of the event will be described in terms of event onset date and event ended date, if known

#### Severity of Adverse Events

All AEs and SAEs will be assessed for severity, according to the Division of AIDS (DAIDS) Table for Grading the Severity of Adult and Paediatric Adverse Events, version 2.1 (July 2017).

The following guidelines will be used to describe severity.

|                                                                                                                                                                                                                                                                      |
|----------------------------------------------------------------------------------------------------------------------------------------------------------------------------------------------------------------------------------------------------------------------|
| Mild (Grade 1): Events that are usually transient and may require only minimal or no treatment or therapeutic intervention and generally do not interfere with the subject's usual activities of daily living.                                                       |
| Moderate (Grade 2): Events that are usually alleviated with additional specific therapeutic intervention. The event interferes with usual activities of daily living, causing discomfort but poses no significant or permanent risk of harm to the research subject. |
| Severe (Grade 3): Events interrupt usual activities of daily living, or significantly affects clinical status, or may require intensive therapeutic intervention. Severe events are usually incapacitating.                                                          |
| Severe (Grade 4): Events that are potentially life threatening.                                                                                                                                                                                                      |

- The Causal relationship of the event to the study medication/IMP will be assessed as one of the following according to the WHO-UMC system for standardized case causality assessment(20):

| Causality term                  | Assessment criteria*                                                                                                                                                                                                                                                                                                                                                                                                                                                  |
|---------------------------------|-----------------------------------------------------------------------------------------------------------------------------------------------------------------------------------------------------------------------------------------------------------------------------------------------------------------------------------------------------------------------------------------------------------------------------------------------------------------------|
| Certain                         | 
 
• Event with plausible time relationship to drug intake
 
• Cannot be explained by disease or other drugs
 
• Response to withdrawal plausible (pharmacologically, pathologically)
 
• Event definitive pharmacologically or phenomenologically (i.e. an objective and specific medical disorder or a recognized pharmacological phenomenon)
 
• Rechallenge satisfactory, if necessary
 
 |
| Probable/ Likely                | 
 
• Event with reasonable time relationship to drug intake
 
• Unlikely to be attributed to disease or other drugs
 
• Response to withdrawal clinically reasonable
 
• Rechallenge not required
 
                                                                                                                                                                                                 |
| Possible                        | 
 
• Event with reasonable time relationship to drug intake
 
• Could also be explained by disease or other drugs
 
• Information on drug withdrawal may be lacking or unclear
 
                                                                                                                                                                                                                           |
| Unlikely                        | 
 
• Event with a time to drug intake that makes a relationship improbable (but not impossible)
 
• Disease or other drugs provide plausible explanations
 
                                                                                                                                                                                                                                                       |
| Conditional/
Unclassified    | 
 
• Event or laboratory test abnormality
 
• More data for proper assessment needed, or
 
• Additional data under examination
 
                                                                                                                                                                                                                                                                           |
| Unassessable/
Unclassifiable | 
 
• Report suggesting an adverse reaction
 
• Cannot be judged because information is insufficient or contradictory
 
• Data cannot be supplemented or verified
 
                                                                                                                                                                                                                                         |

- Action taken
- The outcome of the adverse event – whether the event is resolved or still ongoing
- AEs will be coded according to the MedRA system by medical monitor

